#### Sample size

A combination of techniques will be applied to classify SIS-patients into pathophysiologic subgroups, most of which are newly developed (section 2.3). The acromiohumeral distance (AH) is a recognized parameter related to rotator cuff disease and based on literature it has rather wide inter-individual variations. Therefore, sample size calculation will be based on this parameter.

In a study of Gruber et al., AH values of 9.4 (SD = 3.4) were observed in subjects without diagnosed cuff pathology. A subacromial space narrower than 6 mm on radiographs is considered pathologic and strongly indicative for supraspinatus tendon rupture [46].

The unpaired *t*-test was used to determine the sample size with a difference of AH of 3.4 mm between groups assumed as clinically relevant, comparing AH during abduction task radiographs in patients where humerus cranialisation plays a key-role compared to AH in other subgroups of SIS patients.

Based on the standardized difference: 3.4 mm/3.4 mm = 1.0, a required power of 80% and a p-value of 0.05 for significance, the Altman's Nomogram resulted in 30 shoulders/patients per group.

In our hypothesis, we defined 4 etiological mechanisms. Based on clinical experience and literature, we assume around 30% type III acromion responsible for complaints of SIS,[16] 20-30% of the SIS symptoms are caused by humerus cranialisation and pathologic motion patterns,[47] 15-20% by subacromial inflammatory processes without subacromial narrowing and 5-10% by other impinging structures than the acromion, leaving around 10-30% for a group in which SIS symptoms seem to be caused by two or more hypothesized etiologic mechanisms. With 30 patients needed in the humerus cranialisation subgroup (i.e. 30% of the patients), this leads to a total group size of 100 patients diagnosed with SIS based on patient history, physical examination, radiographs and MRI arthrography.

Additionally, we expect that around at least 25 patients will be diagnosed with another diagnosis than SIS after MRI-arthrography and radiographs [40,48]. These patients can not be included in the SISTIM study but selected patients will be analyzed separately in distinct research projects, if eligible (trial registry numbers:NTR1545 and NTR2282).

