#### Statistical analyses

Patient data, including patient characteristics, physical examination, interview, radiological findings, questionnaires, psychological scores, biomechanical measurements and MRI findings will be entered in a database.

With regards to presence of cranial translation of the humerus as detected on radiographs during rest and abduction and adduction tasks, statistical analysis will be performed by a means of repeated measures ANOVA, with the measure of co-contraction controlled as a confounding factor.

For the isometric Principal Action EMG measurements, data are tested by means of a General Linear Model analysis for repeated measures, controlling for factors Muscle, subacromial anaesthetics, sAH and VAS for pain.

RoM in standardized motions will be analyzed with a General Linear Model analysis for repeated measures, controlling for factors VAS pain, subacromial anaesthetic, dAH and sAH. dAH obtained from 3D-kinematics will be analyzed equally.

Additionally, we will use students' unpaired t-tests to compare continuous variables (e.g. patient characteristics, clinical scores, RoM, dAH) between defined pathologic subgroups.

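### The sample size section does not say whether the cranialisation group is compared with all other patients or with each subgroup; on the second reading, power against subgroup 2c is about 48-76%, not 80%

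*Protocol article*

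**What the plan says.** All the sizing figures are in the Sample size section of the protocol article.

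- The test is an unpaired t-test with a 3.4 mm difference in AH taken as clinically relevant. The comparison is described as "comparing AH during abduction task radiographs in patients where humerus cranialisation plays a key-role compared to AH in other subgroups of SIS patients".
- The inputs are "Based on the standardized difference: 3.4 mm/3.4 mm = 1.0" and "a required power of 80% and a p-value of 0.05 for significance". The result is that "the Altman's Nomogram resulted in 30 shoulders/patients per group".
- The total of 100 follows from needing 30 in the cranialisation subgroup, taken as 30% of patients. No other group is checked against a required size.
- The expected shares are about 30% for hooked acromion (2a), 20-30% for cranialisation (1), "15-20% by subacromial inflammatory processes without subacromial narrowing and 5-10% by other impinging structures than the acromion" (2b and 2c), and the remaining 10-30% or so for patients with two or more mechanisms.

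The Statistical analyses section adds unpaired t-tests of continuous variables "between defined pathologic subgroups".

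**The concern.** A per-group number and a power figure belong to a specific two-group comparison. Here one side of it is clear (cranialisation) and the other is not. The phrase for the comparator can mean everyone else pooled or each other subgroup separately. The per-group wording and the later t-tests between subgroups point to the second meaning. Solving the total from one group only fits the first.

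The choice matters because the expected subgroup sizes differ widely. On the pooled reading the comparator is 70-80 patients and power is ample. On the subgroup reading one comparator, 2c, is expected to hold only 5-10 of 100 patients. A reader who takes 80% power to apply to each subgroup contrast could give a non-significant AH difference between cranialisation and 2c more weight than it can bear. 2c is one of the four hypothesised mechanisms, and the primary goal is to sort patients into these groups as a basis for diagnostic and treatment flowcharts.

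**Working it through.** **Inputs** (Sample size section): difference 3.4 mm; SD 3.4 mm, so d = 1.0; power 80%; significance level 0.05; total 100; the shares listed above. The section does not state whether the test is one- or two-sided; two-sided is assumed throughout.

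**Step 1: the plan's own figure.** The normal approximation for equal groups is n per group = 2(1.96 + 0.84)² / d² = 15.7, so 16. The exact t calculation gives 17. The stated 30 per group is not reproduced: at 30 v 30 the exact power is 96.8%. Thirty is therefore more than 80% power requires, and a subgroup is not underpowered merely because it falls short of 30.

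**Step 2: expected sizes out of 100.** Cranialisation 20-30; 2a about 30; 2b 15-20; 2c 5-10; combination group = the remainder.

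**Step 3: power for unequal groups.** The noncentrality parameter is d / √(1/n₁ + 1/n₂) on n₁ + n₂ − 2 degrees of freedom; power comes from the noncentral t distribution. Example, 30 v 10: 1 / √(1/30 + 1/10) = 2.74 on 38 df, power 76.1%.

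| Comparator | 30 cranialisation patients | 20 cranialisation patients |
|---|---|---|
| 2c, n = 5 | 52.0% | 48.3% |
| 2c, n = 10 | 76.1% | 70.3% |
| 2b, n = 15 | 87.1% | 81.1% |
| 2b, n = 20 | 92.4% | 86.9% |
| 2a, n = 30 | 96.8% | 92.4% |
| All others pooled (70 or 80) | 99.5% | 97.7% |

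The normal approximation is slightly more favourable for 2c: 54.4% and 78.2% against 30, 51.6% and 73.3% against 20. All four values remain below 80%. With 30 cranialisation patients, 2c would need 12 to reach 80% (81.5%; 11 gives 79.0%).

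**Step 4: difference detectable with 80% power against 2c, SD 3.4 mm.** 30 v 10: 3.57 mm; 20 v 10: 3.82 mm; 30 v 5: 4.74 mm; 20 v 5: 4.97 mm. The plan's relevant difference is 3.4 mm.

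**Step 5: the combination group.** It is what is left after the other shares. Its minimum is 100 − (30 + 30 + 20 + 10) = 10, which needs every other share at its maximum, so cranialisation is then 30 and power is 76.1%. If cranialisation is 20, the remainder is at least 100 − (30 + 20 + 20 + 10) = 20 and power is at least 86.9%. Power against this group falls below 80% only when the remainder is near 10.

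**The case against.** The strongest reply is that the 80% is never attached to cranialisation versus 2c. The section describes one two-group test, does not name 2c as a comparator, and fills only the cranialisation group. That is coherent if the comparator is everyone else, because 70 others exceed 30 automatically. This is a fair reading, so it would be wrong to infer that a promised power has definitely been missed. What stands against it is that the text nowhere says the comparator is pooled, while its per-group and plural-subgroup wording allows the other reading.

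The t-tests between subgroups are also only moderate support. They are introduced as additional, no power is claimed for them, and the AH variable they list is the one from 3D kinematics. Radiographic cranial translation is assigned to a repeated-measures ANOVA. The list gives examples, so it does not exclude radiographic AH, but no sentence explicitly plans that contrast against 2c.

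Third, the study is descriptive, and decreased AH is itself one of the features used to characterise the cranialisation group. The practical harm of low power in one AH contrast is therefore limited. That is a reason for modest weight, but not for leaving the powered contrast undefined.

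Two stronger readings are tempting and should be resisted. One is that every subgroup below 30 is underpowered: 2b at 15-20 keeps 81-92%, because 30 exceeds what the inputs require. The other is that the combination group is generally underpowered: that happens only in the corner described in step 5.

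**Conclusion.** The point holds in a limited form. The section leaves its powered contrast undefined, and the answer ranges from ample to inadequate depending on the reading. With all other patients pooled, power is 97.7-99.5%. Taken subgroup by subgroup, power against 2c is below 80% over the whole expected range: 52-76% with 30 cranialisation patients and 48-70% with 20. The gap is small at 30 v 10 and large when 2c is near 5.

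These figures assume a two-sided 0.05 test, a common SD of 3.4 mm, a true difference of 3.4 mm (for the pooled contrast, against the pooled mix of subgroups), and subgroup sizes at the plan's stated shares of 100. They do not show that the study as a whole is too small.

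**What to change.** In the Sample size section:

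- Name AH in cranialisation patients versus all other SIS patients pooled as the contrast that carries the power. Replace the per-group figure with its expected sizes and power: 30 v 70 (99.5%) or, at the low end of the cranialisation share, 20 v 80 (97.7%). State that the test is two-sided, if so.
- Add that the single-subgroup contrast with 2c is expected to have about 48-76% power. Say that it will be reported as an estimate with a confidence interval, and that no conclusion of no difference will be drawn from it.

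The cost is a few sentences, with no extra patients or measurements. The price is that the contrast with 2c can no longer be presented as powered.

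### The total of 100 rests on the upper end of the plan's own 20-30% range for humerus cranialisation, so the 30 patients stated as needed in that subgroup are unlikely to be reached unless the share is close to 30%; power is not at risk

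*Protocol article*

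**What the plan says.** All of the material is in the protocol article, Methods, Study population, Sample size.

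- The calculation is for an unpaired t-test on the acromiohumeral distance (AH): it "was used to determine the sample size with a difference of AH of 3.4 mm between groups assumed as clinically relevant". The contrast is AH during abduction-task radiographs "in patients where humerus cranialisation plays a key-role compared to AH in other subgroups of SIS patients".
- The SD comes from a cited study: "AH values of 9.4 (SD = 3.4) were observed in subjects without diagnosed cuff pathology". The plan continues: "Based on the standardized difference: 3.4 mm/3.4 mm = 1.0", with "a required power of 80% and a p-value of 0.05 for significance". From these inputs "the Altman's Nomogram resulted in 30 shoulders/patients per group".
- On the share of patients in the subgroup it assumes that "20-30% of the SIS symptoms are caused by humerus cranialisation and pathologic motion patterns". It gives about 30% to a type III acromion, 15-20% to inflammatory processes and 5-10% to other impinging structures, which leaves about 10-30% with two or more mechanisms.
- The total follows at once: "With 30 patients needed in the humerus cranialisation subgroup (i.e. 30% of the patients), this leads to a total group size of 100 patients".

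The section adds that at least about 25 further patients are expected to receive another diagnosis after imaging. They are outside the study and cannot fill the subgroup.

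**The concern.** The share is given as a range, and the total then treats the top of that range as the estimate. No reason is given for choosing 30%. The lower end is not a stray figure, because the plan needs it to obtain its 10-30% for the mixed group (shown in the working). So the full range is used for one purpose and only its upper end for the other.

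At stake is whether the plan's only sample-size justification delivers the subgroup size that it calls needed. A study that ended with, say, 22 cranialisation patients would fall short of its own stated requirement, although its planned test would be well powered. There is also a risk in the repair: correcting the share alone would suggest enrolling up to 150 patients when the comparison does not require it.

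**Working it through.** **Inputs (all from Sample size).** Difference 3.4 mm; SD 3.4 mm; power 80%; significance level 0.05, with sidedness not stated and two-sided assumed here; 30 per group; cranialisation share 20-30%; share used for the total 30%; total 100. No loss allowance is stated, so none is applied. Patients are taken as independent.

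**1. The plan's total.** 30 / 0.30 = 100. It reproduces.

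**2. The range behind the mixed group.** With the lower ends: 100 − (30 + 20 + 15 + 5) = 30. With the upper ends: 100 − (30 + 30 + 20 + 10) = 10. This is the stated 10-30%, so the 20% end is in use elsewhere in the same paragraph.

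**3. What 100 patients deliver.** Expected number = 100 × p. Total for an expected 30 = 30 / p. Chance of at least 30 = P(X ≥ 30) with X ~ Binomial(100, p).

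| True share p | Expected in subgroup | P(at least 30) | Total for an expected 30 |
|---|---|---|---|
| 20% | 20 | 1.1% | 150 |
| 25% | 25 | 15.0% | 120 |
| 28% | 28 | 36.4% | 108 |
| 30% | 30 | 53.8% | 100 |

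Even at the most favourable share, reaching 30 is only a little better than an even chance.

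**4. Is 30 per group the requirement?** With standardized difference d = 3.4 / 3.4 = 1.0, the normal approximation gives n per group = 2 × (1.960 + 0.842)² / 1.0² = 15.7, so 16. The exact two-sample t-test gives 16.7, so 17. A one-sided test would need fewer still (13 by the approximation). The stated 30 per group does not reproduce: 30 against 30 has 96.8% power by the t-test, not 80%. A total of about 32 to 34 for both groups would be close to 30, so a nomogram total read as a per-group number is a possible explanation, but the article does not show this.

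**5. Power of the planned comparison with 100 patients** (t-test, d = 1.0, two-sided 0.05). By the plan's shares, the single-mechanism comparators number 30 + 15 + 5 = 50 to 30 + 20 + 10 = 60 if mixed patients are left out.

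| Cranialisation vs comparator | Mixed-mechanism patients | Power |
|---|---|---|
| 20 vs 80 | in comparator | 97.7% |
| 25 vs 75 | in comparator | 99.0% |
| 30 vs 70 | in comparator | 99.5% |
| 20 vs 50 | left out | 96.1% |
| 20 vs 60 | left out | 96.9% |
| 30 vs 50 | left out | 99.0% |

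With everyone else as comparator, 9 against 91 already gives 80.9%.

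**The case against.** The strongest reply is that nothing in the analysis changes. Power is well above the required 80% over the whole range, the plan derives one recruitment figure (100), and it sets no subgroup quota. That stands, and it limits the point to a correction of the text.

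A reader might infer that the study is underpowered or should enrol 120 to 150 patients. The documents do not support this. The larger totals follow only if 30 is a true requirement, and the stated inputs need about 17 per group. The chance of at least 17 among 100 is 81% at a share of 20% and 98% at 25%, and with unequal groups fewer would do.

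A reader might also take the plan to promise that 30 will be available. It does not. It calls 30 needed and presents the shares as assumptions.

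It can further be said that mixed-mechanism patients with cranialisation could be counted in the subgroup, which would make 30 more likely. The plan lists them as a separate share, ties its 30% to the cranialisation subgroup, and gives combination groups their own scenario in the section on relating outcome measures to mechanisms. It does not say, however, how a mixed patient with cranialisation enters this comparison. Treating them as separate is therefore the more natural reading, not a certain one.

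Finally, it is no answer that the matter belongs in a fuller document. The article prints the calculation, and two of its adjacent sentences do not agree.

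**Conclusion.** The point holds as a numerical inconsistency in the sample-size text. The total of 100 uses only the upper end of the assumed 20-30%. On the plan's own range the expected subgroup is 20 to 30, and the chance of at least 30 runs from 1% to 54%. The figure called needed is about twice what the stated inputs require, and for that reason the shortfall costs no meaningful power: it stays above 95% in every split examined.

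The subgroup counts assume independent patients and mixed-mechanism patients kept out of the cranialisation subgroup. The power figures assume a two-sided test, SD 3.4 mm in both groups and no losses. That SD comes from subjects without diagnosed cuff pathology. The plan also uses decreased AH to characterise the cranialisation subgroup (scenario 1 in the section on relating outcome measures), so the outcome is partly built into the groups. High power on AH should therefore be read as a property of the stated calculation, not as wider assurance.

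**What to change.** Do not enrol more. In Sample size:

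1. Replace the requirement of 30 per group by the value that the inputs give, about 17 per group for 3.4 mm, SD 3.4 mm, 80% power and 0.05, and state that the test is two-sided if that is intended.
2. Replace the step from 30 patients and 30% to the total by a statement of what is expected: among 100 patients, 20 to 30 in the cranialisation subgroup at the assumed share of 20-30%.
3. State that power for 3.4 mm then stays above 95% under the listed assumptions (two-sided, SD 3.4 mm in both groups, no losses), and say which comparison applies: mixed-mechanism patients in the comparator (70 to 80 others, about 98% to 99%) or left out (for example 20 against 50 to 60, about 96% to 97%). Say also how a mixed patient with cranialisation is counted.

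The cost is a change of text. Recruitment and measurements are untouched. The downside is that the stated subgroup size becomes less favourable than the 30 now printed.

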### Outcome measures

The included SIS-patients will be subjected to several diagnostic and experimental tests at the LUMC department of radiology (standard and force task radiographs with EMG, MRI-arthrography) and the Laboratory for Kinematics and Neuromechanics (shoulder kinematics, EMG). The set of measurements is described below and outcome parameters are defined, referring to the mechanisms as summarized in out hypothesis and the primary and secondary study goals (A to J).

#### Basic MRI outcomes (study goals A and J)

For the purpose of assessing eligibility criteria and alternative causes of impingement symptoms, an MRI-arthrography is acquired in each patient. MRI's are reviewed by one of two participating musculoskeletal radiologists at LUMC for inclusion and exclusion criteria and standard clinical evaluation. Additionally, MRI scans will be used to identify potential anatomic/structural causes for SIS symptoms and to assess rotator cuff status (muscle volume, presence of tendinosis/tendinitis, intratendinous, bursal or articular side partial tendon tear, Goutallier score for muscle degeneration) [49,50].

*Main outcome parameters*: inclusion/exclusion of patients, alternative diagnoses leading to SIS symptoms, rotator cuff status, signs of anatomical or structural causes for SIS symptoms.

#### 2D radiographical analyses and EMG (B, C, D, J)

Standard anteroposterior shoulder radiographs enable classification of the acromion shape. Patients' acromion Bigliani classification will be assessed: type I (flat), II (curved) or III (hooked) [14]. We expect an incidence of 30% hooked acromions (type III) in SIS-patients [15].

Increased subacromial narrowing during arm abduction has been reported in patients with rotator cuff degradation as a consequence of increased Deltoid muscle activation [27,51-54]. In order to observe and study this potential etiological mechanism, radiographs will be acquired in rest position and during EMG-recorded isometric arm abduction and adduction moment tasks of equal force magnitude, using a set-up with a force sensor and visual feedback (Figure 2). We will quantify the subacromial space using the acromiohumeral distance measure (AH), upward migration index (UMI; similar to AH, but corrected for image magnification and patients bony morphological aspects) [55] and spinohumeral centre method (SHC) [56]. Co-activation of medio-caudally directed adductors during active arm abduction has been reported to reduce this humerus cranialisation and consequent pain in rotator cuff patients [5,51,57-60]. Therefore, muscle activation will be controlled for during the three tasks by simultaneous EMG recording with bi-polar surface EMG of the main arm abductor (Deltoids) and adductors (Latissimus Dorsi, Teres Major, Pectoralis Major).

**Figure 2 F2:**
[figure not shown]
**Set-up for EMG-recorded isometric abduction and adduction force tasks**. Subjects are positioned in front of the radiographic plate, in standing position with the concerning arm in external rotation at his/her side (i.e. hand in frontal plane), enabling the use of this set-up during concomitant acquirement of standard shoulder radiographs. The arm is attached to a 1-dimensional force transducer at the wrist, enabling subject specific force tasks, visual feedback, and equal task force magnitude for abduction and adduction tasks.

The relative activity of the glenohumeral abductors and adductors will be quantified using the "Activation Ratio" [58-60]. The Activation Ratio (AR_muscle_) of each muscle is determined according to its specific primary function. Muscle activation is either 'in-phase' (A^IP^) or 'out-of-phase' (A^OP^) with respect to its primary moment arm. For example, activation of the medial part of the Deltoid (A_DM_) is defined as 'in phase' during active arm abduction tasks and as 'out-of-phase' during arm adduction tasks. Correspondingly, two average EMG levels are determined for each muscle for 'in phase' and 'out-of-phase' activation with respect to the isometric adduction and abduction moment tasks. Based on these data, subject specific Activation Ratios can be calculated for each muscle (AR_muscle_), Eq 1:

$$AR_{muscle}\;=\;\frac{A_{muscle}^{IP}\;-\;A_{muscle}^{OP}}{A_{muscle}^{IP}\;+\;A_{muscle}^{OP}}\;\left[-\;1\;\leq \;AR_{muscle}\;\leq \;1\right]$$

Consequently, AR's of muscles in healthy subjects are positive and close to 1. In subjects with co-activation of arm adductors during abduction tasks, as has been described for the Latissimus Dorsi and the Teres Major in cuff tear patients, AR's of arm adductor muscles are closer to 0 or even negative. Therefore, we expect to find low adductor Activation Ratios in at least a subgroup of SIS patients, in response to reduced AH.

*Main outcome parameters*: Bigliani acromion classification; Acromiohumeral distance (AH) in rest and during abduction and adduction tasks; muscle-specific EMG Activation Ratios (*AR_deltoid_, AR_lattisimus dorsi_, AR_teres mj_, AR_pectoralis mj_*) for quantification of (adductor) coactivation.

